### Secondary outcome measures

#### Pain level assessment

The ESAS at 0^th^, 6^th^ weeks visits will be taken as secondary outcome measures and will be evaluated all the symptoms.

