#### Visits and follow-ups

There will be four visits for the recruited participants during the trial. At the first visit, research investigators will perform the enrollment by checking the eligibility screening, informed consent form, and allocation plan. Then, the blood, saliva, stool, and skin samples will be collected as a baseline and start the treatment as day 1. The next visits will be to assess the adverse drug reaction by a medical officer. At week 6, the blood samples will be collected for assessing the pharmacokinetic parameters. Week-12 visit will be the last visit at which all the participants will be assessed for any adverse reaction, and the blood, saliva, stool, and skin samples will be collected as post-treatment samples.

After the trial, patients will be asked to stop taking cannabis oil from any sources. They will be monitored for another month for withdrawal symptoms.

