#### Trial timepoints

Assessment of adverse drug effects will be collected with 4 time points: 0th, 1st, 6th, 12nd weeks of the trial day. The pain symptoms, QoL and diet pattern will be recorded with 3 time points: 0th, 6th, 12nd weeks. The blood collection (3 mL) for pharmacokinetic and pharmacogenetic tests will be performed on 2 time points: 0th, 6th weeks. The blood (10 mL), feces, skin scrapping, and saliva samples will be taken for biochemistry tests (plasma/ serum), microbiome (gut/ skin/ saliva), cytokines (plasma) and bacterial metabolites (serum/ feces) will be analyzed at 2 time points: 0th, 12nd weeks. The overview of the tests and visits of the clinical trial was shown on the following Table 1.

**Table 1 Tab1:** SPIRIT schedule of enrolment and assessments

#	Timepoint	Week-0 baseline	Week-1 follow-up	Week-6 follow-up	Week-12 follow-up
		T1	T2	T3	T4
1	**Enrolment**				
	Eligibility screening	x			
	Informed consent	x			
	Allocation	x			
2	**Assessment**				
	CRF01 Case Record Form^a^	x			
	CRF02 FW & ADR^b^	x	x	x	x
	CRF03 ESAS	x		x	x
	CRF04 EQ-5D-5 L	x		x	x
	CRF05 Food Frequency Questionnaire	x		x	x
3	**Blood Samples, Serum**				
	Blood Chemistry^c^	x			x
	Cytokines^d^	x			x
	Bacterial Metabolites^e^	x			x
	Pharmacokinetics parameters	x		x	
	Pharmacogenetics parameters	x		x	
4	**Feces Samples**				
	Fecal Microbiome Profile	x			x
	Fecal Bile Acid Profile^f^	x			x
	Fecal SCFAs^g^ and BCFAs^h^	x			x
5	**Skin Samples**				
	Skin Microbiome Profile	x			x
6	**Saliva Samples**				
	Oral Microbiome Profile	x			x

^a^Demographic and Epidemiological Factors: age, weight, height, waist circumference, hip circumference, neck circumference, alcohol consumption, smoking status, occupation, monthly income, method of health payment, and highest education

^b^Follow up and adverse drug reaction: vital signs, physical examination, lab results to assess liver, kidney and heart function, pharmacokinetic record form, drug tolerance assessment form, and adverse event assessment form

^c^Blood Chemistry: lipid profile, liver function test (LFT)

^d^Cytokines: interleukin-17, interferon-gamma, Interleukin-10, tumor growth factor-beta

^e^Bacterial Metabolites: lipopolysaccharide binding protein, sCD14 levels, equol, cadaverine

^f^Fecal Bile Acid Profile: chenodeoxycholic acid, deoxycholic acid, lithocholic acid

^g^SCFAs: butyric acid, propionic acid, acetic acid

^h^BCFAs: iso-butyric acid

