### Primary outcome measures

The pain level of each patient will be assessed using the ESAS form at the last visit as primary outcome.

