#### Biochemical assay

Lipid profile and liver function tests will be measured using the biochemistry analyzer and the quantitative analysis will be conducted as a baseline characteristics.

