## Conclusions

The clinical trial will provide the efficacy of Thai cannabis oils in breast cancer female patients in Thailand, mainly in alleviating chemotherapy-related side effects. Furthermore, it will obtain secondary factors such as QoL indexes, alteration of microbiome profile, bacterial metabolites, and cytokines before and after using the cannabis oil, pharmacokinetic parameters, and pharmacogenetic profiles.

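### The all-symptom ESAS is a listed outcome at weeks 0 and 6 but not at week 12, and the week-12 lipid and liver tests are described as baseline characteristics

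*Protocol article*

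**What the plan says.** The Primary outcome measures section reads: "The pain level of each patient will be assessed using the ESAS form at the last visit as primary outcome".

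Under Secondary outcome measures, the Pain level assessment section reads: "The ESAS at 0^th^, 6^th^ weeks visits will be taken as secondary outcome measures and will be evaluated all the symptoms".

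The Trial timepoints section gives the collection schedule: "The pain symptoms, QoL and diet pattern will be recorded with 3 time points: 0th, 6th, 12nd weeks". Table 1 agrees and marks the ESAS form at weeks 0, 6 and 12. Visits and follow-ups places the week-0 assessment before the first dose: "skin samples will be collected as a baseline and start the treatment as day 1".

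For blood chemistry, a footnote to Table 1 gives the content, "Blood Chemistry: lipid profile, liver function test (LFT", and the table marks weeks 0 and 12. The text of Trial timepoints says that the biochemistry is analysed at both. The Biochemical assay section, which also stands under Secondary outcome measures, says of the same tests that "the quantitative analysis will be conducted as a baseline characteristics".

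The Abstract (Background) states the aim as the intensity of patients' symptoms. The Conclusions say that the trial will provide efficacy, "mainly in alleviating chemotherapy-related side effects".

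**The concern.** An outcome list should tell the reader which measurements, at which visits, will be judged for a treatment effect. This one has two faults.

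- **ESAS.** A value taken before the first dose is named as an outcome, while the end-of-treatment visit is left out for every symptom except pain. The stated aim and conclusion concern symptoms in general, and for those the end of the 12 weeks is the natural time to look.
- **Blood chemistry.** A test repeated after 12 weeks on study oil is described as a baseline characteristic. A week-12 value cannot be one.

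At stake is what can be reported as planned. If week-12 tiredness, wellbeing or anxiety is not a listed outcome, the authors may report it or leave it out once the data are seen, and a reader cannot tell which results were intended. The Statistical analysis section states that there is no correction for multiple analyses, which makes a clear advance list more important.

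**Working it through.** No figure decides this point. The check sets the outcome sections beside the schedule.

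**Step 1. When is ESAS collected?** Weeks 0, 6 and 12 (Trial timepoints and Table 1). Treatment starts after the week-0 baseline (Visits and follow-ups), so there are 3 − 1 = 2 post-baseline ESAS visits.

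**Step 2. Which of these are listed as outcomes?**

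| ESAS content | Week 0 | Week 6 | Week 12 |
|---|---|---|---|
| Pain | secondary | secondary | primary |
| All other symptoms | secondary | secondary | not listed |

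For the non-pain symptoms, one of the two post-baseline visits is a listed outcome. The one that is missing is the end of treatment.

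**Step 3. Is this only the brevity of an article?** No. The section names its visits, and the neighbouring quality-of-life section names weeks 0, 6 and 12. The ESAS list is a stated rule that stops at week 6.

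**Step 4. Which symptoms are affected?** The article's account of the earlier Thai study (Clinical practice in Thailand) reports mean ESAS changes at 1 month of 1.00 for wellbeing, 0.95 for pain, 0.93 for tiredness and 0.85 for anxiety as the largest. Three of these four are non-pain symptoms. This shows which symptoms the team has reason to care about. It does not measure what is lost by omitting week 12.

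**Step 5. What else is listed at week 12?**

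| Measure at week 12 | Status in the article |
|---|---|
| ESAS pain | primary outcome |
| EQ-5D-5L | secondary outcome |
| Adverse reactions (CRF02) | secondary outcome |
| ESAS, other symptoms | collected, not listed |
| Lipids | under the secondary heading, described as baseline |
| Liver tests | as lipids, but liver results are also on CRF02 |

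A Table 1 footnote says that CRF02 includes "lab results to assess liver, kidney and heart function", and the form is completed at weeks 0, 1, 6 and 12.

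**Step 6. Blood chemistry.** Trial timepoints has it analysed at weeks 0 and 12, while Biochemical assay has it analysed as a baseline characteristic. Both cannot describe the week-12 value. The section that follows, on cytokines and bacterial metabolites, states a before-and-after comparison, so the article says so where one is meant.

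**The case against.** The strongest reply is that the article uses pain as shorthand for the whole ESAS. It introduces the earlier study as assessing pain symptoms with the ESAS and then lists wellbeing, tiredness and anxiety. The heading Pain level assessment covers all symptoms. The Summary of the study also describes the ESAS aim as pain intensity. On that reading, the primary outcome takes the whole ESAS at week 12, the secondary outcome takes the other visits, and no gap remains. The Abstract (Methods) also has ESAS assessed before and after the interventions, which suggests that week 12 was intended. This reading is tenable. It does not remove the need for a correction, because the primary outcome would then be an undefined set of symptoms rather than a pain level, and week 0 would still be listed as an outcome.

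A reader might infer more than the documents support:

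- *That the conclusion has no end-of-treatment analysis at all.* Not so. Pain, quality of life and adverse reactions are all listed outcomes assessed at week 12.
- *That liver safety at week 12 is dropped.* Not so. Liver laboratory results are on the adverse-reaction form at that visit, and adverse reactions are a secondary outcome.
- *That the week-12 chemistry has no analysis by arm.* This goes too far. Biochemical assay does not say that baseline is the only use, and Statistical analysis gives paired tests and three-arm comparisons for continuous data in general. What stands is the conflict between two sections.
- *That half of the treatment period goes unassessed for the other symptoms.* Not so. ESAS is collected at week 12. What is missing is its place in the outcome list.

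It is also fair to say that the choice of model and table layout may be left to a full protocol or analysis plan that is not shown. Which visits count as outcomes is stated here, and stated badly.

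**Conclusion.** The point holds as a fault in the outcome list that should be corrected. Read literally, the non-pain ESAS symptoms at week 12 are collected but belong to no listed outcome, a pre-treatment value is listed as one, and the use given for lipids and liver tests conflicts with their week-12 measurement and analysis.

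Its size is one of two post-baseline visits for every non-pain symptom, and the week-12 chemistry of up to 90 randomised patients, with lipids the part mainly affected.

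The ESAS part rests on reading the primary outcome as the pain item. If the whole ESAS was meant, the fault becomes an undefined primary outcome, and the same two sections must still be reconciled. The chemistry part does not depend on that reading. A drafting slip is a likely cause, which makes the correction easy but does not make it unnecessary.

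**What to change.** - **Primary outcome measures:** state whether the primary outcome is the ESAS pain item at week 12.
- **Pain level assessment:** make all ESAS symptoms secondary outcomes at weeks 6 and 12, compare each oil with placebo, and use the week-0 value as the baseline adjustment. This also uses the baseline better than the paired tests and unadjusted ANOVA now named.
- **Biochemical assay:** compare week-12 lipids and liver tests between arms, adjusted for week 0, and keep the week-0 values for the description of baseline.
- **Conclusions:** word the efficacy statement to match the pain primary outcome, with other symptoms as secondary evidence. Under the article's own statement on uncorrected analyses, these would not be concluded as established findings.

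The cost is wording and a few extra tables. Every measurement needed is already in Table 1, so there are no new data, visits or samples.

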#### Assessment for quality of life

The QoL will be collected at 0th, 6th, and 12nd weeks. At each dimension, it has the coefficients of the level of severity utilized for calculating the utility score in accordance with the program of Health Intervention and Technology Assessment Program (HITAP).

#### Follow up for adverse events

Adverse reactions will be examined using the IRB-approved case report form for adverse drug reaction. The severity of the effects will be evaluated using 5-grade system, and the relationship to the study drugs by 4 statuses.

#### Biochemical assay

Lipid profile and liver function tests will be measured using the biochemistry analyzer and the quantitative analysis will be conducted as a baseline characteristics.

#### Quantitative analysis of cytokines and bacterial metabolites

We will assess alterations in various cytokines, bacterial metabolites, and the microbiome. Quantitative measurement of IL-10 and TGF-β as anti-inflammatory cytokines, and IL-17 and IFN-γ as inflammatory cytokines will be conducted with Flow Cytometry analyzer using human essential immune response panel (13-plex). Bacterial markers such as LBP, sCD14, and equol will be detected using ELISA techniques. Bacterial metabolite concentrations, including short-chain fatty acids, bile acids, and cadaverine, will be determined via HPLC. Then, the expression levels of these parameters before and after treatment will be compared to evaluate the efficacy of the treatment.

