#### Microbial abundance and diversity

For the gut, skin, and oral microbiomes, we will compare microbial abundance at the baseline and end of the trial across different treatment arms to investigate how cannabis oil treatment affects pain assessment. The alpha and beta diversity of the microbiota will be analyzed.

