#### Statistical analysis

The data collected from different questionnaires, including case report forms, will be prepared in Microsoft Excel, followed by data cleaning and extraction. The statistical analysis will be performed on an intention-to-treat basis using Stata/MP software version 16.0 (StataCorp 2017, College Station, TX). Descriptive statistics like pair t-tests for before and after-treatment groups will be carried out using mean with standard deviation for normally distributed continuous data and median with interquartile range for non-normal distributed continuous data. Categorical data will be presented as counts and percentages using the Chi-square test. Continuous data will be assessed for normal distribution using a histogram and Shapiro–Wilk test. One-way ANOVA with Bonferroni correction will be used for normally distributed continuous data, and the Kruskal-Wallis test will be used for non-normal distributed continuous data among 3 arms.

To identify the alpha diversity, Shannon’s diversity index is used for evenness and Chao 1 index for the richness of operational taxonomic units (OTUs). The Jaccard dissimilarity index is used to detect beta diversity, and it is statistically described by permutational multivariate analysis of variance using distance matrices (PERMANOVA) test. A statistically significant level is defined as *p* < 0.05. Correction for multiple analyses was not done, but they will not be included in the conclusion of the study as factual findings. Sensitivity analysis using some subgroup to show robustness will be considered if the primary outcome is statistical significance.

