## Discussion

Thailand actively launched cannabis oil in the market in 2018, subsequently, the FDA (Food and Drug Administration) authorized all hospitals running under the Public Health Ministry for medical cannabis to be available on prescription to patients for approved conditions like cancer chemotherapy for relief of pain, to counter inflammation, and so on [32]. The previous clinical trial as nationwide has been approved the effectiveness of the cannabis oil in cancer patients. The current study is a continual clinical trial to obtain additional information and it is expected to improve the chemotherapy-related symptoms, their QoL, and the adverse effects in breast cancer patients.

As some studies have observed distinct gut bacterial and fungal profiles in various breast cancer subtypes [15, 16], our anticipation is to identify a comparable microbial abundance pattern in both hormone-dependent and independent breast cancer patients. Additionally, we aim to detect alterations in these patterns before and after treatment with cannabis oil and placebo oil, with a focus on pain scores. A noteworthy aspect of this study is its comprehensive examination of the microbiota, encompassing the gut, skin, and oral microbiomes in breast cancer patients.

An advantageous aspects of this study are the effective observation of the immunomodulatory role of the microbiota measuring interleukin-17 (IL-17) and interferon-γ (IFN-γ), interleukin-10 (IL-10) and tumor growth factor-β (TGF-β) and the assessment of the alterations at both the baseline and post-treatment stages or within each treatment group. This approach is expected to yield specific insights into cytokine expression in breast cancer patients and reveal improvement following treatment.

The levels of Lipopolysaccharide-binding protein (LBP) and soluble CD14 (sCD14) serve as markers for bacterial translocation, indicating the potential existence of a gut-breast cancer microbiota axis [33]. It is essential to assess the influence of cannabis oil on preventing the bloodstream transmission of oncogenic bacteria through this axis. Additionally, equol, a potent estrogenic metabolite produced by intestinal bacteria [34], Is of interest. The study also aims to establish a distinct profile of bacterial markers in breast cancer patients and gain insights into their characteristics following treatment.

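### For cytokines and bacterial metabolites, efficacy is defined by a before-versus-after comparison that is not tied to the placebo arm

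*Protocol article*

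**What the plan says.** Under Quantitative analysis of cytokines and bacterial metabolites, after listing the markers and assays, the article states: "Then, the expression levels of these parameters before and after treatment will be compared to evaluate the efficacy of the treatment". It names no placebo comparison.

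Statistical analysis contains two kinds of test for continuous data:

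- Within arm: "Descriptive statistics like pair t-tests for before and after-treatment groups will be carried out".
- Between arms: "One-way ANOVA with Bonferroni correction will be used for normally distributed continuous data". Where normality fails, the three arms are to be compared by Kruskal-Wallis instead.

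It does not say which test decides which outcome, or whether the three-arm tests apply to changes or to week-12 values.

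The Discussion describes the cytokine work as "the assessment of the alterations at both the baseline and post-treatment stages or within each treatment group" and expects it to show improvement after treatment. The Conclusions again describe the microbiome, metabolites and cytokines before and after the oil, without mentioning placebo.

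Two other outcomes are worded differently. The primary outcome is a single time point: "The pain level of each patient will be assessed using the ESAS form at the last visit as primary outcome". For the microbiome the comparison is explicitly between arms: "we will compare microbial abundance at the baseline and end of the trial across different treatment arms".

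**The concern.** A paired test within an oil arm asks whether levels in that arm changed. It does not ask whether they changed more than under placebo. Over the 12 weeks every participant is also starting or continuing chemotherapy, under differing regimens. Cytokines, short-chain fatty acids, bile acids and translocation markers could therefore move in all three arms for reasons unrelated to cannabis. Regression to the mean and the passage of time act in the same way.

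Randomisation and the placebo arm exist to remove such shared change, and a before/after efficacy rule does not use them. What is at stake is a claim that the oil alters immune or bacterial markers when the same alteration occurred on placebo.

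**Working it through.** **1. Which comparison does the text prescribe?** The efficacy sentence names before and after, and no arm. The only test under Statistical analysis that takes a before/after pair is the paired t-test. The microbiome section names the treatment arms in its comparison, and the cytokine and metabolite section does not. Taken with the Discussion's reference to assessment within each group, the within-arm reading is the natural one, although the sentence itself does not use those words.

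**2. Inputs for the illustration.**

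- Patients per arm: 30, with up to 50% loss (Sample size estimation). Evaluable per arm: 30 × (1 − 0.5) = 15 at worst, 30 at best.
- Significance level: 0.05 (Statistical analysis). Sidedness is not stated; two-sided is assumed.
- Shared shift: not given for any biomarker. A range of 0.2 to 0.8 SD of the change is assumed. One point in that range can be tied to a figure in the article: ESAS pain in the earlier cohort changed by 0.95 ± 2.39 at 1 month (Clinical practice in Thailand). Reading 2.39 as the SD of the change, 0.95 / 2.39 = 0.40 SD. This is a symptom score, borrowed only for scale.
- Oil effect: none. All three arms shift equally.

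The article gives no error rate for the before/after rule, so there is no stated figure to reproduce.

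**3. Formula.** With shift δ in SD units, the paired t statistic has a noncentral t distribution with n − 1 degrees of freedom and noncentrality δ√n. The chance of a significant result is P(|T| > t), where t is the 97.5% point of the central t distribution.

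- n = 15: t = 2.145. At δ = 0.40 (0.3975 unrounded), δ√n = 1.54, which gives 0.300.
- n = 30: t = 2.045. At the same δ, δ√n = 2.18, which gives 0.558.

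**4. Chance that a given oil arm is significant when the oil does nothing.**

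| Shared shift (SD of change) | 15 evaluable | 30 evaluable |
|---|---|---|
| 0.2 | 11% | 19% |
| 0.40 | 30% | 56% |
| 0.5 | 44% | 75% |
| 0.8 | 82% | 99% |

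**5. Two oil arms.** The chance that at least one is significant is 1 − (1 − p)². At 0.40 SD this is 1 − 0.700² = 51% (n = 15) and 1 − 0.442² = 80% (n = 30). The right benchmark is not 5% but the value with no shift, 1 − 0.95² = 9.75%.

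**6. The between-arm alternative.** A one-way ANOVA on change scores among the three arms was simulated under the same conditions (20,000 trials per setting). It rejected in 4.9% to 5.2% of trials at every shift, because a shift common to all arms cancels.

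**The case against.** The strongest reply is that Statistical analysis already provides ANOVA or Kruskal-Wallis among the three arms for continuous data, calls the paired t-tests descriptive, and says that results not corrected for multiplicity will not enter the conclusions as fact. On that view the efficacy sentence is loose wording, also compatible with comparing changes between arms, and the mapping of tests to outcomes can be left to a fuller plan.

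Much of this stands. The between-arm tests are in the plan, so it cannot be said that the randomised comparison has been discarded. The multiplicity sentence also limits how far a marker result could travel. But nothing assigns the three-arm tests to these markers, while the cytokine and metabolite section does assign efficacy to the before/after comparison. Calling a t-test descriptive does not settle the matter when that section gives the same comparison an efficacy role. The multiplicity sentence concerns the number of tests, not the choice of comparator. This is therefore a rule stated badly, not a detail left out.

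A reader might infer that efficacy throughout the trial is judged within arms. The documents do not support that. The primary outcome is week-12 ESAS pain with no paired test attached, the microbiome is compared across arms, and no within-arm efficacy rule is given for other ESAS symptoms or EQ-5D. The opening of the cytokine and metabolite section does mention the microbiome, but the microbiome's own section states the between-arm comparison.

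A reader might also infer that a false claim for the oil is certain, or that significance on oil without significance on placebo will be taken as proof. The first depends on which test the authors rely on. No section states the second rule.

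**Conclusion.** The point holds for the secondary cytokine and bacterial-metabolite outcomes only. For these, the article defines efficacy by a before/after comparison and does not connect it to placebo. If that rule is followed, shared change can be credited to the oil: over assumed shifts of 0.2 to 0.8 SD, each oil arm has an 11% to 82% chance (15 evaluable) or a 19% to 99% chance (30 evaluable) of a significant result with no oil effect, against about 5% for a between-arm test.

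These figures assume normally distributed changes, the same shift and SD in all arms, and two-sided testing at 0.05. They show the mechanism and do not forecast any particular marker. The direction does not depend on the size chosen: any non-zero shared shift takes the paired test's false-positive rate for an oil effect above 5%.

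**What to change.** In the cytokine and metabolite section, replace the before/after efficacy sentence with a statement that efficacy on each marker rests on the difference between each oil and placebo at week 12, adjusted for the week-0 value, with a 95% confidence interval. A between-arm comparison of change from baseline is also valid; baseline adjustment is a recommendation, not something the documents already state.

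In Statistical analysis, assign that between-arm comparison to these outcomes, and say that within-arm paired results are descriptive and support no efficacy statement. Bring the corresponding Discussion and Conclusions wording into line.

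The same baseline-adjusted analysis could be used for ESAS, EQ-5D and the diversity indices for consistency, but that is optional and corrects no stated rule.

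The cost is wording. Table 1 already schedules cytokines and bacterial metabolites at weeks 0 and 12 without distinction by arm, so no new samples, visits or patients are needed. The change should be made before the data are analysed.
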